## Abstract

**Background:**

The incidence of sick sinus syndrome will increase due to population ageing. Consequently, this will result in an increase in the number of pacemaker implantations. The atrial lead is usually implanted in the right atrial appendage, but this position may be ineffective for prevention of atrial fibrillation. It has been suggested that pacing distally in the coronary sinus might be more successful in preventing atrial fibrillation episodes. The aim of this trial is to study the efficacy of distal coronary sinus versus right atrial appendage pacing in preventing atrial fibrillation episodes in patients with sick sinus syndrome.

**Methods/Design:**

This study is designed as a multicenter, randomized controlled trial. Patients with sick sinus syndrome and at least one atrial fibrillation episode of 30 seconds or more in the six months before recruitment will be eligible for participation in this study.

All participants will be randomized between pacing distally in the coronary sinus and right atrial appendage. Randomization is stratified for all participating centers. Conventional dual-chamber pacemakers with advanced home monitoring functionality will be implanted. The ventricular lead will be implanted in the right ventricular apex. The first three months of the 36-month follow-up period are considered as run-in time. During the pre-randomization visit and follow-up, an interview, electrocardiogram and pacemaker assessment will be performed, prescribed antiarrhythmic medication will be reviewed and patients will be asked to complete an SF-36 questionnaire. An echocardiographic examination will be conducted in the pre-randomization phase and at the end of each follow-up year. Home monitoring will be used to send daily reports in case of atrial fibrillation episodes.

**Discussion:**

This randomized controlled trial is the first in which home monitoring will be used to compare atrial fibrillation recurrences between pacing in the distal coronary sinus or right atrial appendage. Home monitoring gives the opportunity to accurately detect atrial fibrillation episodes and to study characteristics of atrial fibrillation episodes. Should distal coronary sinus pacing significantly diminish atrial fibrillation recurrences, this study will redefine the preferential location of an atrial lead for preventive pacing.

**Trial registration:**

Current Controlled Trials ISRCTN65911661, registered on 8 July 2013.

## Background

Sinus node disease is defined as an intrinsic, symptomatic form of sinus node dysfunction and was first described by Wenckebach in 1923. It is also known as the sick sinus syndrome (SSS) and develops at a mean age of 68 years [1–5].

It is expected that the incidence of SSS will continue to increase due to ageing of the population, as impulse formation within the sinus node declines over time [6]. This may be caused by destruction of the sinus node itself or ischemia, inflammation or degeneration of the surrounding nerves or ganglia. If more than 90% of the sinus node tissue is damaged, SSS develops. However, sinus node dysfunction may also have extrinsic causes including antiarrhythmic drug usage, electrolyte disturbances, hypothermia, hypothyroidism, increased intracranial pressure and excessive vagal tone [6]. Sinus node disease accounts at present for approximately 35 to 45% of the pacemaker implantations in Europe and the United States and it is expected that the number of subjects requiring cardiac pacing will continue to rise in the coming decades [1, 6–9]. Within this group, 30% have symptomatic paroxysmal atrial fibrillation (PAF) [10]. The combination of sinus bradycardia or sinoatrial block and paroxysms of atrial fibrillation (AF) is also known as the brady-tachy syndrome [1, 4]. AF is associated with severe implications including heart failure and stroke; 20% of all strokes can be attributed to AF and patients with AF have a five-fold higher risk of stroke [11].

A meta-analysis by Coplen *et al*. revealed that only 50% of the PAF patients who were treated with anti-arrhythmic drugs remained in sinus rhythm (SR) during a one-year follow-up period [12]. In addition, the heart rate of SSS patients, who already have a sinus bradycardia, will become even lower when using antiarrhythmic drugs for symptomatic episodes of AF. In the PAF study, atrioventricular junctional (AVJ) ablation with DDD pacemaker implantation was compared with pharmacological treatment [13]. Quality of life scores were higher in the non-pharmacological group and these patients were also less symptomatic.

However, AVJ junctional ablation is often considered the final step of AF therapy due to its irreversible nature. Chen *et al*. proposed that catheter ablation of AF can improve sinus node dysfunction, since 95% of the patients did not have a pacemaker indication after the procedure [14]. However, these patients were relatively young and not all patients with severe symptomatic SSS may benefit from this approach. Therefore, preventive pacing could be an appropriate treatment modality for this group of patients.

The aim of the ‘Right versus Left Atrial Pacing in Patients with Sick Sinus Syndrome and Paroxysmal Atrial Fibrillation’ (Riverleft) trial is to study the efficacy of distal coronary sinus (dCS) versus right atrial appendage (RAA) pacing in preventing AF recurrences in patients with SSS and PAF. Characteristics of AF episodes, such as the number and duration of recurrent AF episodes, will be examined and compared between both study arms. The selected pacemaker (Evia DR-T or Eluna DR-T, Biotronik, SE & Co. KG) for the Riverleft study is equipped with home monitoring (HM) technology, which makes continuous assessment of cardiac rhythm feasible [15, 16].

## Methods/Design

### Study design

Riverleft is a multicenter, randomized controlled trial with an inclusion period of approximately two years and a follow-up period of three years for each enrolled patient. An overview of the Riverleft study design is given in Figure 1.

**Figure 1 Fig1:**
[figure not shown]
**Overview of the Riverleft study design.** Eligible patients will be informed about the study and asked to participate. Signed informed consent will be obtained prior to enrollment. In the next phase, the participant will be randomized between right atrial appendage (RAA) pacing and distal coronary sinus (dCS) pacing. A three-month run-in time will start after implantation. Adjustments to pacemaker settings and prescribed medication can be made without any consequences for the study. After finishing the run-in period, adjustments to pacemaker (PM) settings or prescribed drugs are only allowed if necessary. Electrocardiogram (ECG) will be made at each visit, an echocardiogram et the end of each follow-up year. The study will end for each participant after a 36-month follow-up period.

All participating centers will have an appointed local investigator who will be responsible for appropriate inclusion, implantation and follow-up. Furthermore, all centers will have an independent cardiologist, who patients with questions regarding the Riverleft trial can contact.

### Study population

Patients of 18 years or older, with either intrinsic or extrinsic (antiarrhythmic drug-induced) SSS and at least one PAF episode of 30 seconds or more within six months before enrollment, will be eligible to participate in the study. PAF episodes will be assessed by 24-hour Holter recording, preceding enrollment.

All patients with a clinically estimated life expectancy of five years or less or mental and/or physical inability to accomplish the follow-up period, will be excluded from participation in the Riverleft study. Left ventricular ejection fraction of 40% or less, malignancies and congenital heart defects are also exclusion criteria. Furthermore, chronic obstructive pulmonary disease classified as GOLD 4 and renal disease resulting in a glomerular filtration rate of ≤30 mL/min or creatinine value of ≥250 umol/L will prevent candidates from participation. The local investigator will only enroll eligible subjects after a signed informed consent form (ICF) is obtained.

### Sample size

A total number of 300 patients is required to detect a difference with a power of 0.8 between both study arms in recurrences of PAF. To maintain statistical power in case of dropout rates as high as 10%, 330 participants will be enrolled.

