### Randomization

Enrolled patients will be added to a tailor-made website, which will automatically randomize participants to either the control group (RAA pacing) or experimental group (dCS pacing). Randomization is stratified for all participating medical centers.

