### Statistical analysis

This study is designed to compare recurrences of AF episodes between two treatment groups. Therefore the Fisher’s exact test will be used for this categorical data to assess the difference in AF recurrence. Continuous data regarding duration and total number of AF recurrences will be analyzed by the Student’s t-test. Kaplan-Meier curves will be constructed to compare event-free survival between both groups. Secondary outcomes will be analyzed by a multivariate analysis. A *P* value of 0.05 is considered to be statistically significant.

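### Enrolling 330 covers dropout up to about 9%, not 10%: at 10% dropout 297 patients remain, 3 short of the stated 300, with a minor loss of power (about 0.796 against 0.80)

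*Protocol article*

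**What the plan says.** The Sample size section of the protocol article has two sentences. The first gives the requirement: "A total number of 300 patients is required to detect a difference with a power of 0.8 between both study arms in recurrences of PAF". The second gives the allowance for loss: "To maintain statistical power in case of dropout rates as high as 10%, 330 participants will be enrolled".

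Read together, 300 is the number that must remain for the stated power, 10% is the upper end of the dropout allowed for, and 330 is the enrolment meant to bridge the two. The Statistical analysis section sets the significance threshold (a P "value of 0.05 is considered to be statistically significant") without saying whether the test is one- or two-sided. The Randomization section describes allocation to two arms without giving a ratio.

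**The concern.** The second sentence makes a claim that can be checked from the section's own three numbers, and it does not come out. A dropout rate is a share of those enrolled, so an enrolment that protects a requirement of 300 must still leave 300 after that share is removed. Adding 10% to 300 does not do this, because the 10% is later taken from the larger number.

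At stake is the accuracy of a published design figure. The sample-size statement is what a data monitoring board, an ethics committee or a later reader uses to judge whether losses have stayed within plan. As worded, it tells them that 10% dropout leaves the required number in hand, when the limit is nearer 9%.

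**Working it through.** **Inputs, all from the Sample size section**

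- Required number: 300
- Power: 0.8
- Dropout allowed for: up to 10%
- Enrolment: 330

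**Step 1. Reproduce the plan's figure.**

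300 × (1 + 0.10) = 330. This matches exactly, so the requirement was evidently multiplied by 1.10.

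**Step 2. Apply the stated dropout to the stated enrolment.**

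330 × (1 − 0.10) = 297, and 300 − 297 = 3 patients short, or 1% of the requirement.

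**Step 3. Find the enrolment that leaves 300.**

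N = required / (1 − dropout) = 300 / 0.90 = 333.3, rounded up to 334. Check: 334 × 0.90 = 300.6, whereas 333 × 0.90 = 299.7. The difference from the plan is 334 − 330 = 4 patients.

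**Step 4. Find the dropout that 330 does cover.**

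1 − 300/330 = 0.0909, or 9.1%. At 9%, 330 × 0.91 = 300.3, which is enough.

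**Step 5. Size the effect on power.**

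Assumptions not stated in the article: 1:1 allocation, a two-sided 0.05 level, and 300 being exactly the number that gives 0.80. The planned difference is not needed. It is fixed implicitly by the condition that 300 patients give 0.80, and for a normal-approximation test the signal scales with the square root of the number of patients.

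- Signal at 300: 1.960 + 0.842 = 2.802
- Signal at 297: 2.802 × √(297/300) = 2.802 × 0.99499 = 2.788
- Power at 297: Φ(2.788 − 1.960) = Φ(0.828) = 0.796

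**Step 6. Check that this does not hinge on the assumptions.**

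| Setting | Power at 297 |
|---|---|
| Comparison of means, two-sided 0.05 | 0.796 |
| Comparison of means, one-sided 0.05 | 0.796 |
| Comparison of proportions, control rates 0.3 to 0.9 | 0.796 |
| Log-rank comparison, 30% to 100% of patients with an event | 0.796 |

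In each row the effect was first set so that 300 patients give 0.80. Whatever outcome and test the 300 was planned for, the loss is about 0.4 percentage points.

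**The case against.** The strongest reply is that nothing of practical weight is lost. The article states power to one decimal place, and 0.796 rounds to 0.8. The gap appears only at the very top of the allowed range, since any dropout up to 9.1% leaves 300 or more. The figure of 330 is also within about 1.2% of 334 (4/334). All of this stands, and it limits the point to a correction of wording.

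One could also argue that the 10% was meant relative to 300, so that 30 losses are allowed and 330 − 30 = 300. That does explain the figure. But the sentence speaks of a dropout rate in a trial that enrols 330, and the natural base for such a rate is those enrolled. Thirty losses out of 330 is 9.1%.

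Two stronger readings are tempting, and the document supports neither.

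- A reader might infer that power is not maintained and that the trial is underpowered at 10% dropout. The calculation does not bear this out: a fall from 0.80 to about 0.796 is immaterial.
- A reader might infer that the 300 itself is unfounded, because the section speaks only of "required to detect a difference with a power of 0.8" and gives no size for that difference. The article is a condensed account, and its Ethics section refers to a study protocol approved by the ethics committee, which is not shown. The planning assumption may well be there, so its absence from the article is not an error. Working backwards from 300 to a list of detectable differences would not help either: the result depends on a control rate, an allocation ratio and a sidedness that the article does not give, and it would not show what the planners assumed.

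**Conclusion.** The point holds as a minor arithmetic error. On the section's own figures, 330 enrolled with 10% dropout leaves 297 and not 300. The requirement was multiplied by 1.10 where it should have been divided by 0.90. The enrolment that fully covers 10% is 334, and 330 covers 9.1%. No other document can change this, because all three numbers are in the same paragraph.

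Its size is 3 patients and about 0.004 in power. The count rests on no assumption beyond reading dropout as a share of those enrolled who then contribute nothing to the analysis. The power figure also assumes that 300 gives exactly 0.80; if 300 was itself rounded up from a smaller number, the loss would be smaller still or nil. The design and the planned enrolment do not need to change on this account.

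**What to change.** Change the second sentence of the Sample size section in one of these ways:

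- keep 330 and say that it covers dropout up to about 9%;
- keep 330 and say that at 10% dropout about 297 patients remain, with power just under 0.80; or
- keep the 10% and raise enrolment to 334.

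Either of the first two is enough. They cost one sentence and no patients, and the only downside is a slightly less favourable stated figure. The third costs 4 more patients for a negligible gain in power. The Trial status section says that inclusion had not started, so the correction would come before any data.

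Optionally, when editing the paragraph, the authors could report the planning assumption behind the 300 from the full protocol. It should be the assumption actually used, not a difference fitted to 300 afterwards.

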### Primary outcomes

The main objective of this study is to determine the effect of dCS pacing compared to RAA pacing for the prevention of recurrent AF episodes. Total number of AF recurrences and time between recurrences will be assessed and compared between both groups.

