### Secondary outcomes

The relationship between pacing site, reduction of AF episodes, quality of life, heart failure, cerebrovascular accident (CVA), number of cardioversions, frequency and duration of hospital admission and AF progression to persistent AF will be examined.

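### The stated primary outcomes and the stated analyses do not match: two unranked primaries, only one of them with an assigned test, and a power statement that does not say which measure it covers

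*Protocol article*

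**What the plan says.** The protocol article addresses the main comparison in four places.

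- **Primary outcomes:** "Total number of AF recurrences and time between recurrences will be assessed and compared between both groups". No order or priority is given between the two.
- **Statistical analysis:** Fisher's "exact test will be used for this categorical data to assess the difference in AF recurrence". Then: "Continuous data regarding duration and total number of AF recurrences will be analyzed by the" Student's t-test. Then: "Kaplan-Meier curves will be constructed to compare event-free survival between both groups". One general rule follows: a P "value of 0.05 is considered to be statistically significant".
- **Sample size:** the power claim reads "A total number of 300 patients is required to detect a difference with a power of 0.8 between both study arms in recurrences of PAF".
- **Secondary outcomes:** the list opens with "The relationship between pacing site, reduction of AF episodes, quality of life, heart failure", so fewer AF episodes is also a secondary topic.

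**The concern.** A confirmatory trial needs one identifiable comparison that decides the question, and its outcome definition, test and sample size should all refer to it. Here the section that names the primary outcomes and the section that names the tests point to different quantities. The analysis presented first, and linked to the purpose of the design, is a categorical comparison that the primary outcomes do not list. One of the two listed primaries has no method.

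The abstract says that a significant reduction in recurrences would change where atrial leads are preferentially placed. Safety monitoring lets the monitoring board stop the trial for significant benefit. In neither place can a reader tell which result must be significant. If several AF measures are tested at 0.05 and the choice is made later, the false-positive risk exceeds 5% and the choice may look data-driven.

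**Working it through.** **Step 1. Outcomes set against methods.** AF recurrence as categorical data is read here as any recurrence, yes or no.

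| AF measure | Listed as primary | Stated method |
|---|---|---|
| Total number of recurrences | yes | t-test |
| Time between recurrences | yes | none |
| Any recurrence | no | Fisher's exact test |
| Duration | no | t-test |
| Event-free survival | no | Kaplan-Meier curves, no test named |

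Only the first row is complete. Kaplan-Meier event-free survival is ordinarily time to the first event, so it does not supply a method for the gaps between successive recurrences.

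**Step 2. The plan's own figure.** The 300 cannot be reproduced from the article, which gives no effect size, rate or standard deviation. A condensed article may leave those to the full protocol. The point here is only that the measure is not identified. What 300 patients can detect depends on the measure. Assuming 1:1 allocation (150 per arm), two-sided 0.05 and 80% power:

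- any recurrence: a difference of about 14 to 16 percentage points for assumed control rates of 30% to 80% (14 to 17 with continuity correction);
- a mean compared by t-test: a standardised difference of about 0.32.

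**Step 3. False-positive risk if the measures were independent.** The formula is 1 − (1 − 0.05)^k.

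- k = 2 (the listed primaries): 1 − 0.95² = 9.75%
- k = 3 (the measures with a named test): 1 − 0.95³ = 14.3%
- k = 4 (event-free survival added): 1 − 0.95⁴ = 18.5%

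**Step 4. The same risk with correlated measures.** All the measures come from the same episodes in the same patients, so independence overstates the risk. A simulation with no treatment effect used 150 patients per arm and 4,000 runs in each of five scenarios. Episode counts were gamma-frailty Poisson over 2.75 years (months 3 to 36, because run-in episodes are not counted). The mean was 0.7 to 20 episodes per patient and the gamma shape 0.3 or 0.5, which gave 35% to 72% of patients with any recurrence. All these rates are assumptions. So are the choices the article leaves open: total duration per patient, a log-rank test for event-free survival, and a t-test on mean gap in patients with at least two recurrences. The chance of at least one result below 0.05 was:

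- two listed primaries: 9.0% to 9.7%
- three measures with a named test: 9.3% to 11.3%
- those three plus event-free survival: 10.1% to 12.1%

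The simulation error is about √(0.10 × 0.90 / 4,000) = 0.5 percentage points.

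**Step 5. Cost of keeping both listed primaries with a Bonferroni split.** Assume that 300 gives exactly 80% power at two-sided 0.05. At 0.025 each, the size factor is (2.2414 + 0.8416)² / (1.9600 + 0.8416)² = 9.505 / 7.849 = 1.211. Then 300 × 1.211 = 363.3, so about 364 evaluable patients. At 300, power for each falls to about 71%. A single primary needs no change of size on this account.

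**The case against.** The strongest defence has three parts.

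First, a hierarchy, an alpha split or a success rule may sit in the full protocol or the SAP, and its absence from an article is not an error. That stands. It does not remove the mismatch, because the article itself fixes the primary outcomes in one section and different analyses in another. An unseen document cannot make those two sections agree.

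Second, a consistent reading exists. Both the sample size and the opening of Statistical analysis speak of recurrences, and Fisher's test is presented as following from that purpose, so Fisher's test on any recurrence could be the intended main test. That is plausible, and it would be too strong to say that the power can belong to no test. But on this reading the main test concerns an outcome that Primary outcomes does not list, so the conflict remains.

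Third, the size can easily be overstated. A reader might infer four or five primary tests, any one of which lets the trial claim success, with a false-positive risk of 18.5% to 22.6%. The article does not support this. Only two measures are labelled primary and only three have a named test. Time between recurrences cannot be counted as a fifth test when no analysis is assigned to it. The 0.05 threshold is stated generally, and no rule says that one significant result is enough. The higher percentages also require independence, which is implausible for these measures.

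**Conclusion.** The point holds as a contradiction between stated sections. Two unranked primaries are listed, only total number has a matching test, three other measures are analysed without being listed, and the power statement does not identify its measure.

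The consequence for error is moderate. It is about 9% to 10% if the two listed primaries are each tested at 0.05, about 9% to 11% across the three measures with a named test, and 10% to 12% with event-free survival added. These figures assume that each measure is tested at two-sided 0.05, that any significant result would be taken as positive, that allocation is 1:1, and that event rates lie in the simulated range. The mismatch rests on none of these assumptions.

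**What to change.** Before recruitment opens (Trial status says inclusion had not started), align Primary outcomes, Statistical analysis and Sample size.

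1. Choose one AF measure already named as the single primary. Total number of recurrences, per monitored time after run-in, is closest to the present Primary outcomes text, but the choice is the sponsor's. AF burden is not needed here: it appears only in the Discussion and would be a new outcome.
2. Give that measure one matching test at two-sided 0.05.
3. State that the 0.8 power refers to that comparison, and restate the power if it was calculated for a different measure.
4. Test the other listed primary next in a fixed sequence, or make it secondary, in either case with a suitable method.
5. Label the remaining measures (any recurrence, duration and event-free survival if total number is chosen) as supportive.

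The cost is an amendment to an already approved protocol and a check of how the 300 was derived. The sponsor also gives up some routes to a positive headline. If the 300 was calculated for the chosen measure, the number of patients need not change.
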